| 25. Documentation procedure:  - If applicable: reference to CRFs  - Indication of data to be collected  - Sample handling  - Retention / archiving (incl. time limits)  - Access to data and samples | The data collection and the selection of the instruments to be used are based on international standards and are developed in a multidisciplinary process. The final data collection forms will be submitted later.  Collection of primary data happens decentralised in 10 clinics for 2.000 patients. The primary data are to be recorded in electronic case report forms (CRFs) and subsequently merged centrally. The consolidation is done via the data entry and management software secuTrail. A scientific documentalist is planned for the development of data collection instruments, electronic implementation, pseudonymisation, data merging and extraction, data monitoring, data cleaning and plausibility checks. The described evaluation-specific data on emergency admissions and hospital stays will be collected (primary data), and secondary data will be processed. Secondary data will be made available both, the hospital information systems as well as the participating health insurance company. Within the framework of the project, a central, relational database will be set up in which primary and secondary data will be made available in pseudonymised form. The scientific staff of the participating evaluating institutes, as well as the biometrician of the project, are involved in all phases of data collection, processing and evaluation. Quality assurance measures include the training of staff in data collection and technical support for the implementation of electronic data collection on site in the participating EDs, as well as monitoring of data entry and quality on site and centrally.  Two study physicians per study center (n=20) who have used the APU app / process will be interviewed with semi-structured interviews. The only documents recorded are the consent forms for interview participation. Study physicians will be recruited during staff training for the APU app or by e-mail as a letter inviting them to take part in the study with study information (e.g. information on the objective, background and the study protocol): Information about the objective, the background, data protection regulations of the study, as well as an explanation of the interview procedure). The interview will be recorded as an audio file. No personal identifying data of the physicans (or of patients through interview answers) will be collected. The audio files will be transmitted to the transcription company in accordance with data protection regulations, transcribed and transmitted back to the Institute of Medical Sociology and Rehabilitation Research. Interview transcripts are stored in anonymized form with restricted access on the servers of the Charité. The audio files of the interviews will be deleted after receipt of the interview transcripts by the Institute of Medical Sociology and Rehabilitation Research or after completion of the transcription process by the contracted transcription company. A commissioned processing agreement is concluded between the transcription company and Charité in accordance with Art. 28 DSGVO to carry out the transcription of the audio files. Access to this data is only permitted to the responsible staff member in the APU project.  For the participatory observations, n=25 patients will be observed during ED treatment. All data will be collected anonymously by study staff from the Institute of Medical Sociology and Rehabilitation Research, i.e. no personal data will be entered into the observation records, but the application of the new form of care in the "real-life" setting, as well as possible influencing contextual factors (e.g. ED procedures, communication structures, patients, staff, etc.) will be observed and recorded. The anonymous protocols are stored and analysed at the Institute for Medical Sociology and Rehabilitation Research.  Only the principal investigator of the study, as well as the staff in charge of data management, have access to the study data.  The study data will be analysed for up to 2 years after the end of the study funding.  The study data will then be kept for 10 years and then deleted. A corresponding data protection concept is being developed with the official data protection officer of the Charité and other responsible bodies. |
| 26. If applicable: description of how the health status of affected healthy persons is to be documented. | Not applicable. |
| 27. If applicable: methods to identify, document, and report adverse events (when, by whom and how ?). | Adverse events will be recorded during the index stay and telephone follow-up. All adverse events will be reported to the principal investigator within 3 working days. Further reports will be made as required |
| 28. Procedure for protecting the confidentiality of the stored data, documents and, if applicable, samples, description of the pseudonymisation or anonymisation of the data and samples of study participants (initials and date of birth as coding scheme are not permitted!).  - Description of the separation of  medical records, study documentation and allocation of personal data  - Designation of access rights including access to participant identification lists during and after the study  - Detailed specification of the procedures for  transmission, encryption, restriction of processing (blocking) and deletion (including details of the network structure used, if any, and servers used).  -If applicable, access to identifying data for legally authorised auditors (third parties) for the purpose of inspection of the files | The study participants are assigned an automatically generated pseudonym.  The participant identification list is kept locked in the rooms of the respective study teams. Only personnel involved in the study and the study leaders on site have access to these documents. After the study has been conducted, the participant identification list will be stored in a lockable steel cabinet at the site of the study leader for the legally required period of 10 years.  Module 5:  Expert interviews are pseudonymised, as no personal data are collected. After deletion of the audio files, the transcripts are anonymous.  Participant observations are collected anonymously.  The study data (expert & patient data) will NOT be passed on to third parties. |
| 29. Declaration of compliance with data protection  - Assurance that all data collected and stored about the participants will be will be treated confidentially (e.g. medical confidentiality)  - Assurance that the identifying data will be disclosed only to the principal investigator or employees appointed / authorized by him/her.  - Indication of the measures taken to ensure  confidentiality  - Measures to ensure data protection  transmission of data which cannot be which do not allow third parties to establish a personal reference.  - Information on information, revocation, correction and deletion options,  - measures to safeguard the rights of the participants.  - If transfers to non-EU countries are intended: Measures for compliance with data protection (e.g. existence of an adequacy decision by the EU Commission or explicit consent of the participants to such transfers). | All data collected and stored about participants / experts will be treated confidentially (data secrecy and medical confidentiality).  The identifying data are only accessible to the principal investigator and the employees appointed by him/her.  The right to information exists for all collected study data. This means that the participant has the right to gain information and correction or deletion of his/her personal study data at any time. |

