| 4. Subject of the study and its objectives; statement of the hypotheses, separated into main and secondary hypotheses, and of the clinical parameters (primary and secondary endpoints) against which the hypotheses are to be tested. | Patients with atraumatic abdominal pain have a very broad range of diagnoses, therefore, those patients with atraumatic abdominal pain should receive faster, safer and more targeted care.  To assure high quality of care and potentially reduce mortality, it seems imperative to implement a novel management pathway, which standardizes the process from start of care to final diagnosis, disposition and specific therapy of atraumatic abdominal pain patients in the emergency department (ED). Therefore, a team of multidisciplinary experts has developed the „Abdominal Pain Unit“(APU) treatment process based on the Delphi method. With APU care is structured according to symptoms and processes rather than diagnosis. The implementation of a new structured, symptom-based process is necessary because patients present themselves in the ED primarily with a symptom and not with an already existing diagnosis. In this way, the indication quality of the diagnostics carried out is improved and patients can be treated more quickly and efficiently.  This study aims to improve German ED care for patients suffering from atraumatic abdominal pain. An application-supported pathway for the ED will be implemented, which supports quick, evidence-based, and standardized diagnosis and treatment plans for patients with atraumatic abdominal pain in the ED.  We hypothesize that the App-based APU-process will lead to:  1) Shorter duration of treatment at the ED while improving patient-reported outcomes (assessed as acute pain score or/and patient satisfaction) at discharge from the ED; or an  2) Improvement of patient-reported outcomes (assessed as acute pain score or/and patient satisfaction) at discharge from the ED while measuring a constant duration of treatment; or a  3) Shorter duration of treatment and unchanged patient-reported outcomes (assessed as acute pain score and patient satisfaction) at discharge from the ED.  All three scenarios will be interpreted as improvement of patients care by the new pathway.  Primary outcomes:  Acute pain score at discharge from the ED, patient satisfaction at discharge from the ED, duration of treatment in the ED  Secondary outcomes:  Patient safety, process quality, quality of care |

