| 15. Biometric planning with indication of statistical methodology, including power calculation.  Indication of the statistician(s)  (if advice is given by the Institute of Biometry of the Charité, a signature must be inserted) | Justification of the selected case numbers/sample sizes (power calculation).  In the evaluation of a new form of care with a broad focus on improving patient care, there is no single research hypothesis to be tested, but rather a series of combined endpoints (process times, patient-related endpoints). Therefore, no classic sample calculation is possible, as it is usual for confirmatory effectiveness studies. Furthermore, the achievable number of patients is limited by the study centers and the expected proportion of emergency patients with atraumatic abdominal pain. The justification of the sample size is therefore based on feasibility considerations and accordingly a power analysis was performed for relevant endpoints of evaluation modules 1 and 2. A total achievable sample size of 2.000 patients is expected. With a conservative estimate, we expect a loss to follow-up of 15%, since the time of transfer for patients, as well / or the time of outpatient discharge is not always predictable. Moreover, the recording of the endpoints may not be possible in the case of emergency transfers. This means that the expected number of evaluable patients is reduced to at least n=1.700. For the correction of the stepped-wedge design according to Hemming (appendix 4: (Hemming and Taljaard 2016) the following assumptions were made: there are random cluster effects, fixed time effects, but no interactions between cluster and time. Intracluster correlation coefficients (ICC) are usually between 0.01 and 0.02 in human studies (appendix 5: (Killip, Mahfoud et al. 2004). Choosing the conservative variant of an ICC of 0.02, which leads to the highest SWD correction factor on this interval, we obtain a correction factor of 2.71. Applying this correction factor results in an effective total number of cases corresponding to an RCT design of n=627, i.e. n=313 per treatment arm. For the power estimates, the significance level for 3 parallel tests according to Bonferroni is adjusted to α*=0.05/3=0.0167. For the above-mentioned primary endpoints under the respective assumed effect sizes δ and α*, the following numbers of cases would result for an RCT: 1) for δ=0.341 in a 2-sided t-test, n=183 per group, 2) for δ=0.0863 in a Chi² test, n=105 per group, and 3) for δ=0.499 in a 2-sided t-test, n=86 per group are required. The power calculations lead to the result that the study is sufficiently powered for all 3 endpoints with an RCT-equivalent of n=313 patients per treatment arm when testing the 3 test hypotheses defined above. Specifically, a power of 1) 96%, 2) 99% and 3) 99% could be achieved for the assumed effect sizes with the achievable number of cases n=313 per treatment arm corrected for SWD. Especially for the "patient reported outcomes" of endpoints 2 and 3, the assumed number of cases and thus the achievable power would make the adjustment of the evaluations for do not exclude potential confounders such as age and gender from the outset. Power calculations and power estimates were performed with nQuery Advisor 7.0.  Statistician:  [name], Institut für Biometrie und Klinische Epidemiologie, Charité – Universitätsmedizin Berlin  References:  Hemming, K. and M. Taljaard (2016). "Sample size calculations for stepped wedge and cluster randomised trials: a unified approach." Journal of Clinical Epidemiology 69: 137-146.  Killip, S., et al. (2004). "What is an intracluster correlation coefficient? Crucial concepts for primary care researchers." Ann Fam Med 2(3): 204-208. |

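### Scenarios 1 and 2 count better pain or better satisfaction as success without any condition on the other, so a trial with conflicting patient-reported results would meet the stated rule

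*Protocol*

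**What the plan says.** Protocol item 4 lists three primary outcomes: "Acute pain score at discharge from the ED, patient satisfaction at discharge from the ED, duration of treatment in the ED". It then describes three result patterns.

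- Scenario 1: "Shorter duration of treatment at the ED while improving patient-reported outcomes (assessed as acute pain score or/and patient satisfaction) at discharge from the ED".
- Scenario 2: "Improvement of patient-reported outcomes (assessed as acute pain score or/and patient satisfaction) at discharge from the ED", with duration constant.
- Scenario 3: "Shorter duration of treatment and unchanged patient-reported outcomes (assessed as acute pain score and patient satisfaction) at discharge from the ED".

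The reading of these patterns is fixed in the same item: "All three scenarios will be interpreted as improvement of patients care by the new pathway".

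Item 15 (biometric planning) adds only the testing frame: "the significance level for 3 parallel tests according to Bonferroni is adjusted to α*=0.05/3=0.0167". It contains no non-inferiority margin, no requirement that an outcome must not worsen, and no rule for primary outcomes that point in opposite directions. No other item supplies one.

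**The concern.** Duration is constrained in every scenario: it is shorter in 1 and 3 and constant in 2. Scenario 3 also constrains both patient-reported outcomes, joining them with 'and'. Scenarios 1 and 2 join them with 'or/and', so one improvement is sufficient and the second outcome is left free. It may be unchanged or significantly worse, and the scenario is met either way.

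At stake is agreement between the overall conclusion and its components. The rule as written could label as improved care a trial in which one of its own primary outcomes deteriorated significantly. Pain (a numerical rating scale) and satisfaction (ZUF-8) are measured by different instruments under item 10. Item 11c itself mentions that the app could confuse staff and delay treatment decisions. Discordant results cannot be ruled out beforehand, so the rule should say what happens to them.

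**Working it through.** **Step 1: the logic.** Apply the three scenarios literally to each pattern, where A and B are the two patient-reported outcomes in either order.

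| A | B | Duration | Scenario met |
|---|---|---|---|
| better | better | shorter / constant | 1 / 2 |
| better | unchanged | shorter / constant | 1 / 2 |
| better | significantly worse | shorter / constant | 1 / 2 |
| unchanged | unchanged | shorter | 3 |
| unchanged | significantly worse | shorter | none |

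The third row is the problem. The last row shows that scenario 3 would refuse the same worsening. This step uses no numbers, and the finding rests on it alone.

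**Step 2: the plan's own figures (item 15).** The per-test level is 0.05/3 = 0.0167, so z = 2.394 two-sided. The effective size is 1700/2.71 = 627, or 313 per arm. The power behind the stated group sizes is not given; I assume 80% (z = 0.842). With n = 2(2.394 + 0.842)²/δ²:

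- Endpoint 1, "for δ=0.341 in a 2-sided t-test, n=183 per group": 20.94/0.341² = 180.1, so 181 (182 with the t distribution). Power at 313 per arm is 96.9%, against 96% stated.
- Endpoint 3, δ = 0.499: 20.94/0.499² = 84.1, so 85 (86 with the t distribution, as stated). Power at 313 is above 99.9%, against 99% stated.

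These agree closely enough to treat both δ values as standardised differences. I do not dispute the figures.

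**Step 3: can the trial show both directions at once?** Inputs:

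- From item 15: 313 per arm and level 0.0167. Item 15 counts endpoints 2 and 3 as patient-reported, so 0.499 is the planned effect of one of them.
- Assumed: the other outcome truly worsens by 0.2 or 0.341 SD. The protocol gives no such figure; 0.341 is borrowed from endpoint 1 for its size only.
- Assumed: both outcomes are continuous (item 15 plans a chi-square test for endpoint 2), duration has no true difference and is independent of them, and 'constant' or 'unchanged' means not statistically significant.

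The standard error of a standardised difference is √(2/313) = 0.0799.

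- P(A significantly better) = Φ(0.499/0.0799 − 2.394) > 0.999.
- P(duration not significantly worse) = 1 − 0.0167/2 = 0.992.
- P(improvement declared, scenarios 1 and 2 together) ≈ 0.992. Scenario 2 alone needs no significant change in duration either way, so about 1 − 0.0167 = 0.983.
- P(B significantly worse), true worsening 0.2 SD: Φ(2.502 − 2.394) = 0.543; times 0.992 = 0.538.
- P(B significantly worse), true worsening 0.341 SD: Φ(4.266 − 2.394) = 0.969; times 0.992 = 0.961.

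| True worsening of B | Improvement declared as written | Of all trials: declared and B significantly worse | Declared if B must not be significantly worse |
|---|---|---|---|
| 0.2 SD | 99% | 54% | 45% |
| 0.341 SD | 99% | 96% | 3% |

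The last column is the second minus the third. A simulation of 1,000,000 trials with correlation 0, 0.3 and 0.5 between A and B gives the same figures to within 0.2 percentage points. With no true effect on any outcome, the chance of declaring improvement is 0.024 to 0.025 with or without the added condition.

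**The case against.** Four points deserve weight.

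1. **Silence is not permission.** A reader might infer that the protocol accepts a significant worsening, or that its rule overrides one. It says neither. The scenarios speak of patient-reported outcomes in the plural, and the bracket could be taken merely to name the measures of an overall improvement. This stands as a limit on the claim: the fault is a missing exclusion, not an endorsement of harm. It does not remove the fault, because the bracket states how improvement is assessed, and the change from 'or/and' to 'and' in scenario 3 makes the literal reading the more natural one.

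2. **The analysis plan may deal with it.** Item 15 says there is no single hypothesis to be tested, and rules for discordant endpoints are often left to the SAP, which is not at hand. That would answer a complaint about missing detail. Here, however, the protocol does state a success rule and how it will be read, so an SAP adding a condition would be altering it.

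3. **The probabilities depend on chosen effects.** They do. They show that the trial is large enough to detect both directions together, not that such a conflict is likely.

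4. **The worsening would be visible anyway.** Each primary outcome has its own test, so a significant deterioration would be an explicit result. A reader might go further and expect participating sites to be told simply that care improved. Nothing in the protocol says how results will be communicated, so that inference is not supported. What remains is that the overall label would contradict one of its own components.

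**Conclusion.** The point holds as a defect in the stated success rule. As worded, scenarios 1 and 2 can be met while the second patient-reported primary outcome is significantly worse, and no other part of the protocol prevents it.

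The size is conditional. Under the assumptions in step 3, nearly every trial would be called an improvement; roughly half of all trials (0.2 SD) to nearly all (0.341 SD) would carry that label alongside a significant worsening. Neither the worsening nor the treatment of both outcomes as continuous comes from the protocol. The logical point depends on none of these figures. It does not call the sample size or the type I error into question.

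**What to change.** In hypotheses 1 and 2 of item 4, replace the 'or/and' bracket by a two-part condition: at least one of pain score and satisfaction is significantly better, and the other is not significantly worse, each at the adjusted level of 0.0167. Add one sentence: superiority on one primary outcome together with significant worsening on another is reported as a mixed result, not as improvement.

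This needs no margin, no extra data and no change to the sample size. The cost is that improvement can no longer be claimed when results conflict; with no true effects the chance of a claim is practically unchanged. The condition is modest, since absence of significant worsening does not show absence of worsening: at a true worsening of 0.2 SD, about 45% of trials would still be declared an improvement.

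A non-inferiority condition would be stricter, but the protocol sets no margin, not even for 'unchanged' in scenario 3. If the sponsor later sets one there, the same margin could be considered here with its power cost stated. With no true difference in the second outcome, 313 per arm and level 0.0167, the chance of meeting such a condition is Φ(margin/0.0799 − 2.394): about 54%, 77% and 91% for assumed margins of 0.2, 0.25 and 0.3 SD.

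### Two of the three success scenarios require no change in a primary endpoint, but the protocol gives no margin for no change and plans and powers only difference tests

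*Protocol*

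**What the plan says.** Section 4 of the protocol names three primary outcomes: pain score at discharge, patient satisfaction at discharge, and duration of treatment in the emergency department. It then sets out three scenarios.

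- **Scenario 1:** duration is shorter and at least one patient-reported outcome improves.
- **Scenario 2:** at least one patient-reported outcome improves "at discharge from the ED while measuring a constant duration of treatment".
- **Scenario 3:** "Shorter duration of treatment and unchanged patient-reported outcomes (assessed as acute pain score and patient satisfaction) at discharge from the ED".

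The interpretation is fixed in advance: "All three scenarios will be interpreted as improvement of patients care by the new pathway".

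Section 15 (biometric planning) states that "the significance level for 3 parallel tests according to Bonferroni is adjusted to α*=0.05/3=0.0167". It lists three tests with the number of patients each would need: "for δ=0.341 in a 2-sided t-test, n=183 per group", "for δ=0.0863 in a Chi² test, n=105 per group" and "for δ=0.499 in a 2-sided t-test, n=86 per group are required". It labels endpoints 2 and 3 as patient-reported, so endpoint 1 is duration. It concludes that the study is "sufficiently powered for all 3 endpoints with an RCT-equivalent of n=313 patients per treatment arm when testing the 3 test hypotheses" set out earlier in the document, with power of 96%, 99% and 99%.

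Neither section gives a margin, an equivalence or non-inferiority test, or any other rule for deciding that an endpoint is constant or unchanged.

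**The concern.** Scenarios 2 and 3 each contain a claim of no change, and a difference test cannot support such a claim. A non-significant result is compatible with no change, with a small benefit and with a moderate harm. If the planned tests decide whether an outcome is unchanged, the trial could shorten the stay at the cost of somewhat worse pain or satisfaction and still be reported as improving care.

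The Bonferroni correction acts in the wrong direction on these conditions. It guards against false claims of a difference, so a stricter level makes it easier to pass as unchanged.

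The power statement has a related gap. It speaks of the test hypotheses, and two of the three hypotheses in section 4 include a no-change condition. The power figures come from tests of a difference in one endpoint at a time.

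**Working it through.** **Inputs (section 15).** 2,000 patients, 15% loss, correction factor 2.71, α* = 0.05/3 = 0.0167, effect sizes 0.341 and 0.499 for the two t-tests. The factor 2.71 is accepted and was not re-derived.

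**Step 1: reproduce the plan's figures.**
- 2,000 × 0.85 = 1,700. Then 1,700 / 2.71 = 627.3, which is 313 per arm, as stated.
- Effect 0.341, two-sided t-test at 0.0167, 80% power (assumed, because the protocol does not state it): 182 per group against 183 stated. Power at 313 per arm is 96.9% against 96% stated.
- Effect 0.499: 86 per group, as stated. Power at 313 per arm is above 99%, in line with the stated 99%.
- The chi-square figure of 105 per group could not be checked, because the proportions behind 0.0863 are not given.

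The stated power figures for the two t-tests are therefore sound for what they are: power to detect a difference in a single endpoint.

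**Step 2: chance that a true worsening is not flagged.** For one continuous outcome in SD units, SE = √(2/313) = 0.0799 and z(1 − 0.0167/2) = 2.394. A difference must exceed 2.394 × 0.0799 = 0.19 SD to be significant. The probability that a true worsening d is not significantly worse is Φ(2.394 − d/SE).

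| True worsening d | d/SE | Φ(2.394 − d/SE) | Not flagged |
|---|---|---|---|
| 0.10 SD | 1.251 | Φ(1.143) | 87% |
| 0.20 SD | 2.502 | Φ(−0.108) | 46% |
| 0.30 SD | 3.753 | Φ(−1.359) | 9% |

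At an unadjusted 0.05 the figure for 0.20 SD would be Φ(1.960 − 2.502) = Φ(−0.542) = 29%. The Bonferroni level raises it to 46%.

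**Step 3: does the stated power cover the scenarios?** Scenario 1 needs shorter duration and an improvement in at least one of two patient-reported outcomes. Under the protocol's assumed effects, and with independent endpoints, its power is about 0.96 × (1 − 0.01 × 0.01) = 96%. For the no-change conditions of scenarios 2 and 3 no power is given.

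**Step 4: power of a non-inferiority condition at the existing size.** Take one continuous endpoint, no true change, 313 per arm and margin M. Power is Φ(M/SE − z).

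| Margin M (assumed) | One-sided 2.5% (z = 1.960) | One-sided 0.83% (z = 2.394) |
|---|---|---|
| 0.20 SD | Φ(0.542) = 71% | Φ(0.108) = 54% |
| 0.25 SD | Φ(1.167) = 88% | Φ(0.733) = 77% |
| 0.30 SD | Φ(1.793) = 96% | Φ(1.359) = 91% |

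Power of 80% for one such condition is reached at a margin of (1.960 + 0.842) × 0.0799 = 0.22 SD at one-sided 2.5%, and (2.394 + 0.842) × 0.0799 = 0.26 SD at one-sided 0.83%. Scenario 3 has two no-change conditions plus a superiority condition, so its power cannot exceed that of its weakest condition.

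**The case against.** **The protocol never says that non-significance defines unchanged.** This stands. The link is an inference from the only tests described, and those tests appear in a power justification. A statistical analysis plan, which was not at hand, may set margins. What remains is that the protocol itself fixes the success rule and the power statement. A margin added elsewhere would not make the stated power apply to the no-change conditions.

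**The study is not classically confirmatory.** Section 15 does say that there is no single hypothesis and that the sample size rests on feasibility. It nevertheless uses a multiplicity-adjusted level, refers to test hypotheses and claims adequate power for them, and section 4 attaches a fixed verdict to the result. The objection softens the point without removing it.

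**The power statement may mean only the three endpoint tests.** That reading is possible, because the sentence also refers to the three endpoints. A reader might infer that the stated power applies to none of the scenarios. The figures do not support that, since it roughly holds for scenario 1 under the assumed effects.

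**Larger harms would be caught.** Correct: a worsening of 0.30 SD in one continuous outcome is missed in only about 9% of trials. A reader might infer that any real worsening will be declared an improvement. The arithmetic supports only that a small or moderate one can be.

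**Joint percentages for both patient-reported outcomes are tempting but do not follow from the plan.** One of the two is to be tested by chi-square, so treating both as continuous and independent does not match the planned tests. The figures above are therefore given for one continuous outcome at a time.

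**Conclusion.** The point holds in a limited form. Section 4 makes a constant duration and unchanged patient-reported outcomes part of success, while section 15 plans and powers only difference tests. If the no-change conditions are judged by those tests, a worsening of 0.10 SD in a continuous outcome would pass as unchanged in about 87% of trials, and one of 0.20 SD in about 46%. The stated power is not shown for the no-change conditions of scenarios 2 and 3.

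These figures rest on the protocol's 313 per arm and on its correction factor. The sizes of worsening and the margins are assumptions for illustration, because the protocol gives none and does not say what change would matter clinically. The calculations do not apply to the endpoint tested by chi-square.

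**What to change.** In sections 4 and 15:

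1. For each endpoint that a scenario requires to be constant or unchanged, pre-specify a non-inferiority margin on the scale on which that endpoint is analysed. For the endpoint tested by chi-square this is a risk difference. Give the clinical reason for each margin.
2. Declare the condition met only if the confidence limit on the unfavourable side excludes the margin, and state the one-sided alpha. The table in the working shows how much this choice matters.
3. Limit the power statement to the single-endpoint difference tests. Report power for scenarios 2 and 3 separately from the existing sample size, using the chosen margins.

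The cost is a short revision of the text, with no extra patients. The price is that the stated power for scenarios 2 and 3 becomes less favourable: at a margin of 0.20 SD a single continuous no-change condition has about 71% power at one-sided 2.5% and about 54% at one-sided 0.83%.

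### The three primary endpoints are planned with single-step Bonferroni; Holm's step-down procedure keeps the same 5% error and never has less power (optional, cost-free improvement)

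*Protocol*

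**What the plan says.** Item 15 contains the protocol's only statement on multiplicity: "For the power estimates, the significance level for 3 parallel tests according to Bonferroni is adjusted to" 0.05/3 = 0.0167. The same item explains that several combined endpoints are studied, and concludes: "Therefore, no classic sample calculation is possible, as it is usual for confirmatory effectiveness studies". It nevertheless ends by calling the study sufficiently powered for testing its three hypotheses at 313 patients per arm.

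Item 4 names three primary outcomes: acute pain score, patient satisfaction and duration of treatment in the ED. It then lists three scenarios, which differ in whether duration, the patient-reported outcomes or both improve, and adds: "All three scenarios will be interpreted as improvement of patients care by the new pathway". In scenario 2 duration must stay constant; in scenario 3 the patient-reported outcomes must be unchanged.

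The order of the endpoints in item 15 is not spelled out. Since endpoints 2 and 3 are called patient-reported there, endpoint 1 must be duration.

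**The concern.** Single-step Bonferroni tests each endpoint at 0.0167 whatever the other two show. Holm compares the smallest p-value with 0.05/3, then the next with 0.05/2, then the last with 0.05, and stops at the first failure. Its first step is the Bonferroni test, so it never loses a rejection that Bonferroni makes. Like Bonferroni, it needs no assumption about the correlation between endpoints.

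Decisions on single endpoints matter here because item 4 sorts the result by which endpoints changed. A missed duration effect can move the result from scenario 1 towards scenario 2, and a missed patient-reported effect can move it towards scenario 3. The tests are two-sided, so the same holds for harm: a patient-reported worsening that is detected would rule out scenario 3.

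**Working it through.** **Inputs, all from item 15.** Overall level 0.05 over 3 tests. Effective sample size: "Applying this correction factor results in an effective total number of cases corresponding to an RCT design of n=627, i.e. n=313 per treatment arm". Duration: "for δ=0.341 in a 2-sided t-test, n=183 per group". Endpoint 2: "for δ=0.0863 in a Chi² test, n=105 per group". Endpoint 3: "for δ=0.499 in a 2-sided t-test, n=86 per group are required". Stated power is 96%, 99% and 99%. The stepped-wedge factor of 2.71 is taken as given.

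**The plan's own figures.**
- 2,000 × 0.85 = 1,700; 1,700 / 2.71 = 627; half of that is 313 per arm.
- Target power is not stated; 80% fits. By noncentral t at level 0.0167, duration needs 182 per group (stated 183) and endpoint 3 needs 86 (stated 86).
- Power at 313 per arm is 96.9% for duration (stated 96%) and above 99.9% for endpoint 3 (stated 99%).
- For endpoint 2 the degrees of freedom and rates are not given. A total of 105 per group is obtained only if δ is read as a squared effect size with 7 degrees of freedom. On that squared reading, power at 313 exceeds 99.9% for 1 to 7 degrees of freedom.

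**Family-wise error.** With three independent true nulls at 0.0167, the error is 1 − (1 − 0.05/3)³ = 4.92%. Simulation gives the same value for Bonferroni and Holm: 4.92% at correlation 0, 4.76% at 0.3 and 4.22% at 0.6. Where only some nulls are true, Holm uses the slack that Bonferroni leaves. For example, with one true null beside two planned effects the error is 4.96% against 1.67%, still within 5%.

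**Power for duration at the planned effect.** Power is approximately Φ(δ√(n/2) − z). Here √(313/2) = 12.51, so the noncentrality is 0.341 × 12.51 = 4.27.
- Level 0.05/3 (z = 2.394): 4.27 − 2.394 = 1.87, giving 96.9% (97.0% in simulation).
- Level 0.05 (z = 1.960): 4.27 − 1.960 = 2.31, giving 98.9%.

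The other two planned effects are almost always significant, so Holm nearly always tests duration at 0.05 and attains 98.9%. For the other endpoints, a stated power of 99% leaves at most one point to gain; on the recalculated power the gain is under 0.01 points.

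**If effects or effective sample size are smaller.** The effects in this table are assumptions and do not appear in the protocol; 0.205 is 60% of 0.341. All three endpoints are treated as standardised differences, with 313 per arm and 1,000,000 simulated triples.

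| Assumed effects (SD) | Correlation | Quantity | Bonferroni | Holm |
|---|---|---|---|---|
| Duration 0.205, others 0.30 | 0 | duration | 57% | 71% |
| same | 0.3 | duration | 57% | 71% |
| All three 0.25 | 0 | each endpoint | 77% | 85% |
| same | 0.3 | each endpoint | 77% | 84% |
| same | 0 | all three | 45% | 67% |
| same | 0 | at least one | 98.8% | 98.8% |

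The last row is equal by construction, because Holm's first step is Bonferroni.

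**The case against.** The strongest reply is that nothing in item 15 is wrong. Bonferroni is valid, it gives a conservative power estimate, and the choice between single-step and step-down testing can properly be left to an SAP that is not shown here. Under the protocol's own assumptions the gain is about two points on one endpoint. Item 4 counts all three scenarios as improvement, so moving between them need not change the overall claim. All of this stands, and it is why the point is optional. What remains is that the only method the protocol names has a uniformly better replacement that needs no added assumption.

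Three stronger readings are tempting, and the document does not support them.
- *The final tests carry no adjustment.* Because 0.0167 is tied to the power estimates, a reader might infer three tests at 0.05, with an error of 1 − 0.95³ = 14.3% if independent. But item 15 uses 0.0167 to conclude that the study is adequately powered for testing its three hypotheses, so the natural reading carries that level forward, and the SAP may say so.
- *Success is any one significant endpoint.* Item 4 is not a plain union: scenarios 2 and 3 also require the other side to be constant or unchanged.
- *Holm gains materially on every endpoint.* At the planned effects it does not; the larger gains need the assumed smaller effects.

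**Conclusion.** This is a free improvement of optional severity, not a defect. If the three primary tests are run at 0.0167 each, Holm dominates: 5% family-wise error under any dependence and never less power per endpoint. The size is about 97.0% to 98.9% for duration at plan, and next to nothing for the patient-reported endpoints. In the assumed weaker cases it is 57% to 71% for duration and 77% to 85% per endpoint. These figures rest on 313 effective patients per arm, hence on an ICC of 0.02 and the factor 2.71, and on normal-theory tests; the weaker cases also rest on effects that the protocol does not state. The benefit lies in which endpoints and which scenario can be claimed, not in whether any endpoint is significant. Neither procedure shows that an outcome is constant or unchanged, and a non-significant result should not be taken as showing no change.

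**What to change.** State in item 15, or in the SAP before outcome data are seen, that the three primary endpoints are tested at an overall two-sided 5% with Holm: smallest p-value against 0.05/3, the next against 0.05/2 and the last against 0.05, stopping at the first non-rejection. Base the item 4 claims of improvement or worsening on these decisions, and say separately how constant and unchanged will be judged. Keep the Bonferroni power figures as conservative planning values.

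The cost is one sentence, with no extra patients or data. The one small drawback is that simultaneous confidence intervals matching Holm are less simple; Bonferroni-level intervals can be reported instead.
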